### Participant timeline {13}

A schedule of activities pre-intervention and post-interventions is shown in Fig. 2 (SPIRIT figure).

**Fig. 2 Fig2:**
[figure not shown]
Trial design summary

### Sample size {14}

Hayes and Bennett’s method was used in the sample size calculation for the primary outcome (malaria incidence in children aged between 6 months and 10 years) [34]. Based on data from a previous trial in a nearby area, the mean number of malaria episodes per child per year in the reference arm was assumed to be 1.2 with a between-cluster coefficient of variation of 0.29 [35]. Malaria case incidence in children under 10 years of age was reduced by 54% in Interceptor® G2trial arms in both Benin and Tanzania cRCTs at 12 months [12, 13] and by 47% in the PBO-py LLIN arm in Tanzania compared to py-LLINs in the first year [12]. In an area of higher resistance, intensity models have shown that impact of the PBO-py LLIN may be lower [36]. Hence, we have assumed that the interventions will reduce malaria incidence by 35% (i.e. to 0.78 cases). With a follow-up of 12 months, to detect this impact with 80% power would require follow-up of 45 children (plus 5 more children to account for potential losses to follow-up) in 11 clusters in each of our arms. No adjustment for multiplicity of testing has been included in the sample size estimations because the proposed designs and treatments test different research hypotheses [37, 38]. This results in a total of 33 clusters required for the trial and a cohort of 1650 children.

Sample size considerations take into account the clustered design [34] using prevalence of infection in each study arm as the secondary outcome, based on a superiority design. It was assumed that malaria prevalence in the reference arm has a mean of 50% with a coefficient of variation of 0.29 [35]. With 50 individuals per cluster and 11 clusters per arm, the study will have 80% power to detect a relative 35% lower prevalence (prevalence ratio 0.65) between each intervention arm compared to standard LLIN.

### Recruitment {15}

Each cluster will comprise one village with a minimum of 100 households and with a minimum of 100 children under the age of 10 identified during the census to increase the chances of recruiting sufficient numbers of study participants. A town hall meeting about the research project and activities will be conducted in all village clusters in the presence of health district leaders and at the regional level at the beginning of the project. To ensure support and that communities are well-informed on the trial, meetings will also take place at village level with community representatives. Village leaders and community health workers will be involved in each with the project team to insure adherence of all the population. Consent will be sought from hamlet leaders and household heads to ensure we achieve an adequate sample size. Research assistants, community health workers, and study nurses will be fully trained on the trial and always be available to answer any questions concerning the study.

## Assignment of interventions: allocation

### Sequence generation {16a}

Restricted randomisation will be used to allocate the 33 clusters into the three study arms. Important variables will be balanced between the three study arms (baseline malaria infection prevalence in children aged 0.5 to 10 years, cluster-level LLIN usage (prior to distribution), socio-economic status and village size). The randomisation method will allow us to limit the difference of these selected variables between the arms. At least 10,000 sequences will be generated and one will be randomly picked using a random number generator.

### Concealment mechanism {16b}

Nets will be identified using coloured loops and bales specific to the net type. Randomisation will be performed using the loops to identify the net types to ensure the statistician doing the randomisation is blinded to the allocation.

### Implementation {16c}

The cluster allocation sequence will be generated by the study statistician and the unblinded sequence held by an independent statistician.

## Assignment of interventions: Blinding

### Who will be blinded {17a}

Cluster inhabitants, trial participants (and their care providers where appropriate), data collectors (field staff who will collect mosquito and blood samples), and the study’s data analyst will be blinded. Cluster assignment will be listed by the color of the bale for each of the nets to ensure field implementers are also blinded to the net types.

### Procedure for unblinding if needed {17b}

The data will be shared with the DSMC who can request unblinding from the unblinded statistician if they have any concerns.

## Data collection and management

### Plans for assessment and collection of outcomes {18a}

#### Census

A pretested, short questionnaire including name of the head of the household, number of people living in the house, and the number of children in each age group (0–5 years, 5 to 10 years, 10 to 15 years, over 15 years)) will be administered. The census will be used to estimate the number of LLINs required to be distributed in each house and to randomly select children for the cohort and participants in the cross-sectional surveys. Every building of each village will be mapped using the Global Positioning System (GPS) function on a smartphone.

#### Cohort monitoring

All the children in the cohorts will be cleared of infection at the beginning of the enrollment by giving an artemisinin-based combination therapy. During enrollment visits, detailed questionnaires will be administrated collecting information about socioeconomical status, housing type, and results of the clinical examination. In the subsequent visits, a questionnaire will also be administered to inquire about LLIN usage the night before the visit, any adverse events encountered and travel history since the last visit. Cohort visits will take place every 2 weeks during the malaria transmission season and every 4 weeks during the dry season. A child will be considered ‘lost to follow-up’ if they miss at least 4 visits in a row (i.e. 8 weeks of follow-up time). Any child diagnosed with malaria will be provided with treatment following national guidelines.

In order to estimate malaria transmission in the broader study population, passive case detection will take place in health clinics located within catchment areas of the study clusters. Registration documents already in place in the health clinics include collecting data regarding the village of residence, age, pregnancy status, and gender- and whether they received a malaria test and the result of the test. This data will be collected from health clinics by study team members every 3 months and entered into an Open Data Kit (ODK) form.

#### Cross-sectional surveys

We will conduct three cross-sectional surveys, one prior to the distribution of the LLIN (baseline survey) and two (6 and 12 months) after LLIN distribution. Fifty randomly selected individuals from each study cluster will be examined for malaria infection during each cross-sectional survey. The survey will consist of (1) a household survey and (2) a clinical survey. During the household survey, a questionnaire will be administered to obtain information on possible risk factors for malaria and the randomly sampled person will be tested for malaria using an RDT, regardless of symptoms. A drop of blood will also be used to make microscopy slides to be assessed by study nurses and to be blotted on to filter paper, to detect antibodies to mosquito salivary peptides.

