**Methods:**

This is a three-arm, superiority, triple-blinded, cluster randomised trial, with village as the unit of randomisation. This study conducted in Côte d’Ivoire will evaluate the efficacy on epidemiological and entomological outcomes of (1) the control arm: MAGNet® LN, which contains the pyrethroid, alpha-cypermethrin, (2) VEERALIN® LN, a net combining the synergist PBO and alpha-cypermethrin, and (3) Interceptor® G2 LN, which incorporates chlorfenapyr and alpha-cypermethrin, two adulticides with different mechanisms of action. A total of 33 villages with an average of 200 households per village will be identified, mapped, and randomised in a ratio of 1:1:1. Nets will be distributed at a central point following national guidelines with 1 net for every 2 people. The primary outcome of the trial will be incidence of malaria cases (confirmed by rapid diagnostic test (RDT)) in a cohort of 50 children aged 6 months to 10 years in each cluster, followed for 12 months (active case detection). Secondary outcomes are cross-sectional community prevalence of malaria infection (confirmed by RDT) in the study population at 6 and 12 months post-intervention (50 randomly selected persons per cluster), vector density, entomological inoculation rate (EIR), and phenotypic and genotypic insecticide resistance at baseline and 12 months post-intervention in 3 sentinel villages in each treatment arm.

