### Eligibility criteria {10}

Thirty-three clusters will be included in this study based on the following criteria: being within a 2-h drive from Tiebissou town and at least 2 km away from other included clusters (in order to avoid cross-contamination), an estimated malaria prevalence of over 50% during baseline survey, and the acceptance of the hamlet leader and population.

The cohort will enroll randomly selected children (aged 6 months to 9 years old) who are resident in study villages and whose parents/caregivers have given written informed consent for their child to be included in the study. Children who are expected to be non-resident over the period of study will be excluded.

During cross-sectional malaria prevalence surveys, a maximum of 2 randomly selected household members who have resided in the village over the preceding 3 months, and who provide written informed consent for adults and parental/caregiver consent (and assent for children above 10) for children will be included. Vacant or unfound dwellings, severely ill inhabitants, and the absence of an adult capable of consenting will be reasons for exclusion.

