### Relevant concomitant care permitted or prohibited during the trial {11d}

At enrolment into the cohort, all children will be cleared of malaria infection using artemisinin combination therapy (ACT), irrespective of malaria rapid diagnostic test (RDT) results. During cohort follow-up visits, malaria infection will be detected using the RDT and positive children will be treated according to national guidelines. Children will also be examined by study nurses during each follow-up visit for signs of other illnesses and will be treated if possible. There are no prohibited concomitant treatments.

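### Cohort children, who receive study treatment, remain eligible for the 6- and 12-month prevalence surveys: a small effect on the all-age outcome, a larger one in the under-10 analysis

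*Protocol article*

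**What the plan says.** Under Census, one list is used to select at random both the cohort children and the survey participants. Under Cross-sectional surveys, "Fifty randomly selected individuals from each study cluster will be examined for malaria infection during each cross-sectional survey". Eligibility criteria {10} admits "a maximum of 2 randomly selected household members who have resided in the village over the preceding 3 months", subject to consent, and lists its reasons for exclusion. Cohort membership is not among them.

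The abstract describes "a cohort of 50 children aged 6 months to 10 years in each cluster". In the concomitant care section {11d}, "At enrolment into the cohort, all children will be cleared of malaria infection using artemisinin combination therapy (ACT"), whatever the RDT result. Visits follow every 2 weeks in the transmission season and every 4 weeks in the dry season.

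The protocol gives two accounts of testing at those visits. Section {11d} says infection is detected by RDT and positive children are treated, with no fever condition. Table 1 has the RDT taken only with fever or a recent history of fever.

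Nets are distributed before enrolment {11b}, and children are followed for 12 months. Both post-distribution surveys, including the 12-month one named as the main prevalence comparison, therefore fall within cohort follow-up or at its very end.

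**The concern.** The surveys are meant to show what the nets do to infection in the community. A cohort child's chance of testing positive also depends on the enrolment course and on repeated detection and treatment by study nurses. If such children are surveyed, measured prevalence falls below what the community would show.

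Treatment may also be unequal between arms. The sample size section plans 1.2 episodes per child-year in the reference arm and 0.78 in an intervention arm. Reference-arm children would then be treated about 1.2/0.78 = 1.54 times as often, which pushes cohort prevalence in the two arms towards each other.

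At stake are the level of community prevalence, the arm contrast, and above all the planned analysis by age group {20b}, because the cohort is drawn entirely from young children.

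**Working it through.** **Inputs from the protocol.** "It was assumed that malaria prevalence in the reference arm has a mean of 50% with a coefficient of variation of 0.29" and "With 50 individuals per cluster and 11 clusters per arm, the study will have 80% power to detect a relative 35% lower prevalence", so p0 = 0.50, p1 = 0.325, k = 0.29, m = 50, c = 11. Cohort: 50 children per village. Village size: "A total of 33 villages with an average of 200 households per village". Study setting {9} gives 116,321 people in 110 villages, or 1,057 per village, which at 200 households is 5.3 per household. Recruitment {15} sets a floor of 100 households, "with a minimum of 100 children under the age of 10 identified during the census".

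**Assumptions.** Two-sided 5% test (no level is stated); trial villages like the department average; the cohort prevalences below.

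**Step 1: the plan's own figure.** Hayes-Bennett, with V = p0(1−p0)/m + p1(1−p1)/m + k²(p0² + p1²):

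- V = 0.0050 + 0.0044 + 0.0210 + 0.0089 = 0.0393
- c = 1 + 7.849 × 0.0393 / 0.175² = 11.07
- power at c = 11: Φ(√(10 × 0.175² / 0.0393) − 1.96) = Φ(0.83) = 79.7%

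The stated 80% is reproduced, with no margin.

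**Step 2: share of the survey frame.**

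- Average village: 50/1,057 = 4.7%, about 2.4 of the 50 surveyed. With 4 to 7 persons per household the share is 6.25% to 3.6%.
- Minimum-size village: 100 × 5.29 = 529 people, 50/529 = 9.5%; with 5 per household, 10%.

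**Step 3: mix and recompute.** Measured prevalence in an arm is (1 − f) × community prevalence + f × cohort prevalence. For an average village (f = 4.7%):

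| Cohort prevalence (assumed) | Measured | Difference (points) | Ratio | Power |
|---|---|---|---|---|
| As community | 50.0% v 32.5% | 17.5 | 0.650 | 79.7% |
| Halved in both arms | 48.8% v 31.7% | 17.1 | 0.650 | 79.3% |
| Zero in both arms | 47.6% v 31.0% | 16.7 | 0.650 | 78.9% |
| 25% in both arms, k kept at 0.29 | 48.8% v 32.1% | 16.7 | 0.658 | 77.1% |
| 25% in every cluster | 48.8% v 32.1% | 16.7 | 0.658 | 78.8% |
| 32.5% in both arms, k kept at 0.29 | 49.2% v 32.5% | 16.7 | 0.661 | 76.5% |

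In the fifth row cohort prevalence does not vary between clusters, so the between-cluster SD is multiplied by (1 − f).

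If every village were at the minimum size (f = 9.5%), halving gives a difference of 16.7 points and 78.9% power. A cohort prevalence of 25% in both arms gives 47.6% v 31.8%, ratio 0.667, and power of 74.2% with k kept at 0.29 or about 78% with no cluster variation in the cohort.

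**Step 4: the under-10 stratum.** The cohort share is 50/100 = 50% at the floor of 100 children, and 50/300 = 17% if a village has 300 (assumed). Applying the planned 50% v 32.5% to this stratum as an illustration:

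- 50% share: halving gives 37.5% v 24.4% (difference 13.1, ratio 0.65); 25% in both arms gives 37.5% v 28.8% (difference 8.8, ratio 0.77).
- 17% share: halving gives 45.8% v 29.8% (difference 16.0, ratio 0.65); 25% in both arms gives 45.8% v 31.3% (difference 14.6, ratio 0.68).

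**The case against.** The strongest reply is that this is a condensed article: how survey lists are drawn may be settled in the full protocol or an operating procedure, and randomly chosen cohort children do belong to the all-age study population. The first part stands as a caveat. The article does, however, state the sampling source, the eligibility criteria and the exclusions, and under those rules cohort children can be drawn.

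The second reply concerns mechanism. Under Table 1, symptomless infections in the cohort are not cleared after enrolment, yet the survey counts them. One ACT course about a year before the 12-month survey would not be expected to hold prevalence down where transmission is this intense. This stands: the strength of the effect depends on which account of testing applies, and a reader should not infer that cohort prevalence reflects follow-up instead of the net.

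The third concerns size. A reader might infer that the prevalence ratio is necessarily diluted, or that power drops to about 74%. Neither is supported. Proportional lowering leaves the ratio at exactly 0.65. The 74% needs all 33 villages at minimum size, against a stated average of 200 households, plus a 25% cohort prevalence that has no source in the protocol and between-cluster variation kept at its full relative size.

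Nor does the overlap suggest a false claim of superiority. Any convergence acts towards no difference, village size is balanced in the restricted randomisation, and the baseline survey precedes enrolment and is unaffected.

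**Conclusion.** The point holds, with a modest effect on the all-age outcome. As written, about 5% of the survey sample in an average village, and 9 to 10% in a minimum-size one, can be children under study treatment.

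In an average village, measured reference-arm prevalence falls by about 1 to 2.5 points, the absolute arm difference by 0.4 to 0.8 points, and power by about 0.5 to 3 points. The ratio stays at 0.65 or moves to about 0.66, the latter only if treatment brings cohort prevalence in the arms closer together. The planned incidence figures support that direction, but nothing in the protocol fixes its size.

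The material exposure is the under-10 analysis, where cohort children may be 17% (assuming 300 under-10s) to 50% (at the minimum of 100) of the stratum.

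These sizes rest on a two-sided 5% level, department-average village size and assumed cohort prevalences. The two accounts of testing at visits must be reconciled before the effect can be judged more closely.

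**What to change.** Remove cohort children from the 6- and 12-month survey frames, and sample by the age bands already collected in the census so that the all-age mix is kept. Because the cohort is itself a random draw, the remaining under-10s still represent their age group.

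State in one place whether the RDT at cohort visits depends on fever, so that section {11d} and Table 1 agree.

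If the surveys have already been drawn, record cohort membership for each person surveyed. Report the prevalence comparison without cohort children, weighted back to the age mix, as a sensitivity analysis, and do the same for the under-10 subgroup.

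The cost is a filter on the census list. The downside is fewer eligible young children in small villages, which is why age-band sampling or weighting is needed. Numbers should suffice: a minimum-size village needs about 50 × 100/529 = 9 surveyed under-10s and has 50 outside the cohort.

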#### Entomology activities 

Entomological data collection will include collecting malaria vectors in each cluster every 2 months via HLCs. Data will be generated to calculate mean vector density and EIR for each arm in the trial.

The cross-sectional entomological monitoring will be done in all the clusters. Each cluster will be visited once every 2 months. Survey collections will take place during one night in 6 households in each of the clusters. In each survey, the six households will be selected at random from a census list of households in each study cluster at each timepoint and a description of the household will be recorded on a tablet. The questionnaire will include information on the number of inhabitants, type of house (wall, roof, number of rooms, number of sleeping places, etc.), and presence of animals. Collections will be done by HLC indoors and outdoors. We will use four volunteers for each household collection night, two indoors and two outdoors, with takeover in midway of the collection process during the night. Mosquito collections will run from 18:00 to 08:00 the next morning. The person doing the indoor catches will sit in the living room of the house and the one outdoors will sit on the veranda. The HLCs will be carried out using an aspirator. The volunteers will be lay-persons selected from the study villages and will be fully trained in the HLC activities.

Mosquitoes caught will be counted and identified using a species key based on morphological traits [39, 40]. A subset of the captured female *Anopheles spp* vectors belonging to the *An. gambiae* complex, *An. funestus*, and *An. nili* groups will be stored in individual capsules and kept for sibling species by PCR [32, 41, 42] and sporozoite analysis by PCR [31]. A subsample of *Anopheles* from each cluster will be stored in RNA-later® to compare metabolic enzyme profiles between arm and over time.

To determine insecticide resistance profiles at baseline and at 12 months post intervention, *Anopheles* larvae will be collected from 3 clusters per trial arm c, reared to adult and exposed to different insecticides. WHO cylinder tests and CDC bottle bioassays will be performed using diagnostic concentrations (DCs) of alpha-cypermethrin, PBO + alpha-cypermethrin, and chlorfenapyr. In addition, CDC resistance intensity bioassays for alpha-cypermethrin and PBO + alpha-cypermethrin (5, 10 or higher x DD) will be performed. Whole transcriptomic characterisation (RNA-seq) will be used to identify highly over-expressed genes per phenotype and will form the basis of site-specific qRT-PCR panels for post-intervention (and wider population-level) resistance monitoring. Illumina whole genome sequencing will be used to identify genetic variants (single-nucleotide polymorphisms and/or copy-number variants), associated per phenotype and will form the basis of site-specific amplicon-seq panels for post-intervention (and wider population-level) resistance monitoring.

#### Quality assurance of LLINs

At the beginning and end of trial, we will conduct cone bioassays using a laboratory colony of susceptible *Anopheles gambiae* Kisumu strain to evaluate quality of the LLINs when they are new. Five nets per types will be randomly selected. From each of the LLINs selected, one net piece measuring 30 cm × 30 cm will be cut from each side. Fifty *An. gambiae* (Kisumu strain) will be tested per selected net (total of 250 females per treatment arm). A separate piece cut from the selected net will be sent to Gembloux (Belgium) for chemical testing.

### Plans to promote participant retention and complete follow-up {18b}

After enrolment into the cohort, every reasonable effort to complete follow-up will be made by the study staff within each cluster. The staff will make home visits and use alternate contact information to determine the whereabouts of the child. The projected loss to follow-up rate is 10% and the sample size has been inflated to account for this. Site study staff will develop and implement local standard operating procedures to achieve the projected follow-up rate.

